Fetuses with impaired intrauterine growth often suffer from long term placental insufficiency and subsequent chronic hypoxia not dissimilar from infants suffering from acute perinatal injury with subsequent hypoxic ischemic injury. Many IUGR infants tend to not tolerate labor secondary to their inability to withstand the transient drops in placental blood flow that accompanies normal labor. As a group these infants are twice as likely to have low apgar scores, twenty times more likely to suffer from encephalopathy, five times more likely to suffer perinatal stroke, and ten times more likely to die in the neonatal period [16-18]. Furthermore, these fetuses have a 2 to 3 fold increased risk of delivering prematurely placing them at additional risk of long term morbidity and mortality [19]. MR imaging in premature infants suffering from IUGR show decreased intracranial volume, abnormal diffusion of the posterior limb of the internal capsule, decreased cerebral gray matter, and reduced hippocampal volume that persists through term when compared to gestational aged matched controls [20, 21]. Magnetic resonance spectroscopy in these infants displays elevated lactate and creatine in the white matter, further indicating hypoxemic and nutritional injury. In long term neurodevelopmental follow up patients born with IUGR have an increased risk of developing cerebral palsy and continue to have deficits in learning, cognition, and attention up through adolescence [22-28]. These findings are more pronounced when focusing on the more severe end of the IUGR spectrum, those with evidence of abnormal umbilical flow (absent or reversed end diastolic flow) or birth weight < 3rd percentile [29-31]. This central nervous system injury is likely mulifactorial, with mechanisms such as altered placental flow, repeated hypoxemia, elevated cortisol levels from alterations of the hypothalamic-pituitary-adrenal (HPA) axis regulation, nutritional deprivation, and acidosis after birth all contributing [18, 32]. Given that the majority of infants with IUGR are diagnosed prenatally by standardized ultrasound measurements (usually end of the 2nd trimester) this population represents an ideal model for testing the impact of a prenatal neuroprotectant.

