Preliminary studies in our laboratory have been undertaken in two phases of a previously approved protocol (IRB #201111063). The first phase was undertaken with healthy pregnancies in their last three weeks of pregnancy taking 8oz of pomegranate juice to ensure that it crossed the placenta. In this study, we confirmed placental transfer of polyphenols with HPLC detectable maternal and cord blood levels rising after two weeks on pomegranate juice. In addition, placenta from 4 women who received pomegranate juice in their last 2 weeks of pregnancy demonstrated decreased expression of heat shock proteins (HSP) in the pomegranate group as compared to controls. For phase II of this study (IRB #201111063) we randomized 41 mothers who were pregnant with infants with a diagnosis of IUGR by fetal ultrasound to receive 8oz pomegranate juice or 8oz apple juice. We were able to undertake MRI scans in 30 infants due to problems with preterm birth or movement on the MRI. On this analysis, the infants born to pregnant mothers who drink 8 oz of pomegranate juice daily in the last trimester of pregnancy demonstrated improved diffusion measures in the brain of their newborn infant representing more mature white matter microstructure and improved brain growth (see figures 1-6 below). Of importance, none of the mothers in the IUGR study had placental examination to determine the possible mechanism of benefit of pomegranate juice in pregnancies complicated by IUGR. This current study will fill this important gap in our knowledge.

[figure not shown]
Figure 1: Pilot data in IUGR Trial in 41 mothers randomized to receive pomegranate or apple juice

[figure not shown]

[figure not shown]
Figure 2: Placental pathology with expression for Heat Shock Protein (HSP 90) in women following labor who received 8 oz of promegranate juice compared to control in women without IUGR.

Figure 3: Cord blood levels of polyphenols at the time of birth in women in the randomized trial who received pomegranate juice (pink) or apple juice (yellow). Note the marked elevation in the levels of two polyphenols in the cord blood of infants whose mothers received pomegranate juice.

[figure not shown]

[figure not shown]

[figure not shown]

[figure not shown]

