***Patient population:*** Placentas will be collected after delivery from all pregnancies randomized to the four study groups described above. Systematic random sampling (34, 35) of placentas midway between the chorionic and basal plate and excluding the placental edge, in area 5 B from our published work (36) will yield five specimens for formalin fixation, random orientation in paraffin blocks, and microscopic analyses below. Five separate specimens will be frozen in liquid nitrogen and prepared in Tri-Reagent for protein, RNA and DNA analysis. This number of samples controls for random variation in the placental tissue.

**Analyses to be conducted:** We will evaluate the structure, cellular composition, and expression of selected markers of oxidative stress in the placentas collected from the pregnancies of this study. W*e* have extensive experience in all aspects of the collection, morphometry, micrography, immuno- histochemistry, enzyme immunoassays, RNA and protein analyses of placental tissues.

1: Gross structure of the placenta.We will obtain the placental weight, width (short axis), breadth (long axis), thickness (average of three equidistant measurements perpendicular to the cross section of the chorionic and basal plates of the placenta), and volume of the placenta by water displacement. We also will photograph the chorionic plate to validate the cord insertion site and vascular pattern on the chorionic surface, as this is related to placental function.

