2: Morphometry of villous tree:We will quantifythethree types of villi (stem, intermediate, and terminal). A morphometric grid intersects tissue and cell structures to offer volume density expressed as cm3, while the lines that intersect tissue offer assessments of surface density, expressed as m2. Each placenta provides five embedded samples that are arranged in a tissue array on a single slide. Twenty digital images at 200 X final magnification are obtained from random fields and grids with a spacing of 40µm are overlain on each image for analysis. NIH Image J software (<http://rsbweb.nih.gov/ij/>) and point and line intersects mentioned above are recorded and volumes and surface areas, respectively, of placental items of interest. The morphometry analysis will quantify the relative contributions of the three villous sub-types allows us to test the hypothesis that pomegranate enhances the number of terminal villi (i.e. exchange related villi), compared to control, and that POM juice and POM extract are equal in their effects on the villous development.

3: Assessment of cellular components within villi. We will assess each villus for the relative contributions of trophoblasts by cytokeratin 7 staining, fetal blood vessels (endothelial lectin expression), connective tissue (collagen staining; macrophage immunostaining), and fibrin as a second series of evaluations to test our above hypothesis of less collagen and increased vasulature.

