4: Assessment of trophoblast biology**.** *Proliferation index* in cytotrophoblasts will be evaluated by immunohistochemical staining for Ki67 antigen, which is a marker for cells that are progressing through the cell cycle. *Apoptosis* will be assessed by immunoblot analyses and immunohistochemical staining for the cl-Cyt18 and cl-Parp, as cytoplasmic and nuclear markers of apoptosis, respectively. An apoptotic index for syncytiotrophoblast and cytotrophoblasts will be calculated by dividing the fraction of positive staining cytotrophoblast by the total number of cells, or positive areas in syncytiotrophoblast normalized to surface density of this component from the morphometry evaluation. We additionally quantify the levels of cl-Cyt18 and cl-Parp by immunoblot analysis of extracts from previously frozen placental villi, with actin as a loading control. *Differentiation* will be assayed using IHC to detect hCG and hPL, both specifically produced by trophoblasts. The immunofluorescence stained expression of these hormones in syncytiotrophoblast will be quantified using confocal microscopy of tandem sections to the ones used for morphometry, as an assessment of trophoblast differentiation. Villous tissues will be evaluated by RT-PCR analysis of mRNA and western immunoblot analysis for both hCG and hPL again normalized using actin as a loading control..

5: Assessment of oxidative stress in villous tissues. We will quantify the markers of exogenous stress by immunoassay, immunohistochemistry, or western immunoblot. Each of the chosen dependent variables for this analysis assesses different components of ROS generation. *Heat shock protein 90* will be assessed by immunohistochemistry and western immunoblot analysis.

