Figure 6: Surface based renderings of prematurely born infants (five infants left side) and one term born infant (right) demonstrating marked differences in the surface brain development.

[figure not shown]

[figure not shown]

Perinatal data will also be collected. Items will include:

- Birth weight
- Gestation
- Apgars, resuscitation needed in DR and cord gas characteristics
- Any markers of neonatal illness related to admission to an intensive or special care unit such as encephalopathy, need for intravenous or parenteral nutrition or any related morbidities of preterm birth, e.g. intraventricular hemorrhage.

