**Biostatistical Analyses**

**General methods:**

The statistical methods employed in this study will be complex and will be undertaken with the assistance of [name], biostatistician in the Department of Pediatrics. Clinical data such as maternal risk factors, birth weight, placental weight, gestation, need for resuscitation in the DR, etc. will be collected for both the intervention and the control group during the perinatal course.

The primary outcomes will be either a) brain injury or b) delayed development at 18-24 months. The relationship of placental function and measures to these outcomes will be explored to understand the mechanism of neuroprotection.

Brain injury will be defined as any of the following (see Table 3):

- Moderate to severe injury by qualitative scoring of WMI or GMI
- Diffusion scores (ADC, FA) > 2 SD from normal term infants
- Spectroscopy showing elevated lactate and decreased NAA (hypoxic injury) over the L basal ganglia
- Bottom 25% percentile in brain metrics, volumetric indices, or measures of surface based morphology (SBM) compared to the general healthy population.

Delayed development will be classified as:

- BSID III (MDI or PDI) > 2 SD (< 70) below the normal population

* MRS- MR Spectroscopy; SBM- Surface-based morphology

Table 2. Definition of CNS Injury by US/ MRI

| **Modality** | **Technique** | **Measures** | **Likelihood of injury** | **Definition of**  **Injury** |
| --- | --- | --- | --- | --- |
| Ultrasound |  | Grade IVH | Low | Grade 2-4 |
| MRI | Qualitative | WMI, GMI | Low | Mod-Severe injury |
|  | Diffusion/Spect | ADC, FA  Lactate, NAA | High  Low | > 2 SD above term  Lactate ↑, ↓NAA |
|  | Metrics | Intraparietal diameter, extra cranial space | High | Bottom 25% of the population |
|  | Volumetric | Total volume,  Cerebral gray matter volume, | High | Bottom 25% of the population |
|  | SBM | Cortical surface area, average sucal depth, integrated folding index | High | Bottom 25% of the population |

Continuous variables will be compared using a student t-test when they are parametric and Mann-Whitney test when they are nonparametric. Categorical variables (such as moderate or severe white matter injury) will be compared using either a chi-squared (for parametric) or a Kruskal-Wallis test for nonparametric one way analysis of variance. This is a pilot study where the results will assist in the planning of a larger randomized controlled trial.

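### The raw placental comparison estimates the total effect of assignment; it cannot by itself show a direct placental benefit or harm, and labour, mode of delivery and freezing time are not itemised for collection

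*Protocol*

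**What the plan says.** - **Who is analysed.** Placental Evaluation, Patient population: "Placentas will be collected after delivery from all pregnancies randomized". Nothing restricts or stratifies by labour, mode of delivery or gestation.
- **What is measured.** Item 5 of the placental analyses: "We will quantify the markers of exogenous stress by immunoassay, immunohistochemistry, or western immunoblot". The markers are heat shock protein 90 (HSP90), lipid hydroperoxide, nitrotyrosine, paraoxonase 1 and superoxide dismutase. Item 2, on villous morphometry, aims to "test the hypothesis that pomegranate enhances the number of terminal villi".
- **How it is compared.** Biostatistical Analyses, General methods: "Continuous variables will be compared using a student t-test when they are parametric and Mann-Whitney test when they are nonparametric". No covariate or stratum is named.
- **How it is read.** The Overview of the Placental Evaluation sets a hypothesis about tissue: that the active agents alter villous structure, blunt outside stimuli, or both. Interpretation of results says that more oxidative stress, more fibrin, or fewer terminal villi than control would be noted as adverse effects of the extract.
- **What is recorded at delivery.** The perinatal list has birth weight, gestation, "Apgars, resuscitation needed in DR and cord gas characteristics", and markers of neonatal illness. Outcome measures add preterm labour (as a pregnancy complication) and gestation at delivery. Table 1 has a maternal data row at birth that is not itemised. Labour at delivery, mode of delivery and time from delivery to freezing are not named.
- **Background.** The section on the IUGR model attributes poor tolerance of labour to the fetus's "inability to withstand the transient drops in placental blood flow that accompanies normal labor". The legend of pilot Figure 2 describes "expression for Heat Shock Protein (HSP 90) in women following labor", in pregnancies without IUGR.

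**The concern.** Tissue taken after delivery carries the effects of the pregnancy and also of the delivery. By the protocol's own account, labour interrupts placental flow and growth-restricted fetuses often cope badly with it. Premature delivery is also two to three times more likely in this population, so gestation at delivery will vary. Both labour and gestation at delivery arise after randomisation, and the intervention may change either; gestation at delivery is itself a listed outcome.

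If either differs by arm and affects a marker, the raw difference combines any action of the juice on the tissue with the effect of different delivery conditions. As a measure of what assignment does, that is acceptable. It does not separate the two components, yet the villous hypothesis and the interpretation paragraph treat the difference as pomegranate acting on the placenta. Mechanism is a stated reason for this trial: the protocol says it fills a gap left by the earlier IUGR study, which had no placental examination. A diluted or inflated mechanistic signal could therefore mislead the planning of the larger trial.

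**Working it through.** The protocol gives no power, effect size or SD for any placental measure, so there is no stated figure to reproduce. The calculations below only give scale.

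**Inputs from the protocol.** 80 women randomised 1:1, so 40 per arm (all placentas assumed available).

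**Assumed inputs.** Two-sided alpha 0.05 and 80% power; labour effect on a marker 0.5 to 1.0 SD, with larger values as a stress test; difference in labour rate 20 points, with 30 as a stress test; villous slope 0.1 to 0.3 SD per week of gestation; gestation SD 2.5 weeks. The unit is the marker's SD within labour and gestation level.

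**1. What the trial can detect.** (1.960 + 0.842) × √(2/40) = 0.63 SD. Power for 0.5 SD is 61%.

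**2. Shift from labour.** Shift = labour effect × difference in labour rate: 0.5 × 0.20 = 0.10 SD and 1.0 × 0.20 = 0.20 SD. If labour is commoner under pomegranate and raises the marker, a direct benefit of 0.5 SD appears as 0.5 − 0.10 = 0.40 SD or 0.5 − 0.20 = 0.30 SD.

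**3. What reversal would need.** The shift must exceed 0.5 SD. With a 20-point difference the labour effect must exceed 0.5/0.20 = 2.5 SD; with 30 points, 0.5/0.30 = 1.67 SD. Both lie outside 0.5 to 1.0 SD.

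**4. Shift from gestation.** One week longer × 0.1 to 0.3 SD per week = 0.10 to 0.30 SD of apparent villous gain.

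**5. Simulation** (4,000 trials per scenario, 40 per arm, unadjusted t-test). For a stress marker, a positive difference points to harm; for a villous measure, to benefit.

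| Scenario | Direct effect | Mean raw difference | Significant result |
| --- | --- | --- | --- |
| Labour 50% v 50%, effect 1.0 SD | 0 | −0.01 SD | harm 2.3% |
| Labour 50% v 70%, effect 0.5 SD | 0 | +0.10 SD | harm 6% |
| Labour 50% v 70%, effect 1.0 SD | 0 | +0.20 SD | harm 13% |
| Labour 50% v 50%, effect 1.0 SD | −0.5 SD | −0.50 SD | benefit 51% |
| Labour 50% v 70%, effect 1.0 SD | −0.5 SD | −0.31 SD | benefit 23% |
| Labour 40% v 70%, effect 2.0 SD | −0.5 SD | +0.10 SD | harm 5% |
| Gestation 1 week longer, 0.1 SD/week | 0 | +0.10 SD | benefit 6% |
| Gestation 1 week longer, 0.3 SD/week | 0 | +0.31 SD | benefit 19% |

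The nominal rate is 2.5% in each direction. With equal labour rates or equal gestation the raw test keeps it.

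**6. Does adjustment repair it?** If nothing unmeasured links labour to the marker, a model with arm and labour returns the direct effect (about 0 or −0.50 SD in the rows above). If an unmeasured fetal reserve both makes labour more likely and lowers the marker, it does not. With zero direct effect, labour 50% v 67% and a labour effect of 1.0 SD, the raw difference was +0.17 to +0.18 SD and the adjusted one still +0.08 to +0.14 SD. Adjustment is informative but not decisive.

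**The case against.** The strongest reply is that nothing is wrong with the randomised comparison. The specific aim is the impact of the juice on placental function, and an unadjusted comparison of randomised arms estimates that impact without bias. Labour and gestation at delivery are possible pathways of the treatment, so a difference that runs through them is part of its effect. This stands. A reader might infer that the raw contrast is biased or should be replaced; the documents do not support that.

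A reader might also infer that pomegranate could be made to look harmful despite a true benefit. That needs a larger imbalance or labour effect than the range assumed here. The documents do not say that labour raises these markers, that terminal villi increase with gestation, or that more fetuses would go through labour under pomegranate. Less preterm labour under pomegranate could push the other way.

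Third, a reader might infer that labour will go unrecorded. The lists are open-ended: the perinatal list is not presented as complete, the general methods end their examples with an et cetera, and Table 1 schedules maternal data at birth. So labour is not itemised; it is not shown to be omitted.

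Fourth, supplementary covariate models may sit in a statistical analysis plan not seen here, and gestation at delivery is already collected. That is fair, and it largely answers the gestation half of the point. It does not settle data capture: an analysis plan cannot use a freezing interval that nobody noted. The placental hypothesis and its interpretation stand in the protocol itself.

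**Conclusion.** The point holds in a limited form. The raw placental contrast is valid for the total effect of assignment. On its own it does not support the tissue-level hypothesis, the claim that pomegranate increases terminal villi by acting on the placenta, or the label of adverse effect for a higher stress marker.

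Under the stated assumptions the part due to delivery conditions is about 0.10 to 0.20 SD for labour and 0.10 to 0.30 SD for one week of gestation, against a detectable difference of 0.63 SD. For labour that means dilution of a 0.5 SD benefit, not reversal. Direction and size are assumptions throughout; if labour and gestation turn out equal between arms, the issue disappears.

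Priority is modest. The declared primary outcomes are brain injury and delayed development, the link from placental measures to them is to be explored, and no decision rule depends on these contrasts.

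**What to change.** 1. Add to the perinatal data list: labour (none or present, and duration), mode of delivery, and the interval from delivery to freezing of the tissue.
2. Keep the randomised contrast as the main placental analysis, with gestation at randomisation as a baseline covariate. It is fixed before treatment and known from the dating and entry criteria.
3. Report results by labour status and by gestation at delivery as a supportive sensitivity analysis only. State that both arise after randomisation and that an adjusted estimate may remain biased. Let no claim depend on agreement between the models.
4. Reword the villous hypothesis and Interpretation of results so that an arm difference is described as the total effect of assignment and not, by itself, as a direct placental benefit or adverse effect.

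The cost is a few delivery fields, one supportive model and a few sentences. The freezing interval cannot be recovered later if it is not noted at the time, so the data list should change first.

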**Interpretation of results:** We expect pomegranate-exposed placentas to show less evidence of oxidative stress, more trophoblast mass, and less evidence of fibrin deposition microscopically and by immunoblotting. We expect less apoptosis and more evidence of trophoblast differentiation in the pomegranate group. We will consider any differences in the light of biological significance, also, as small statistically significant differences may prove relevant to the infant outcomes. Although highly unlikely based on the known effects of pomegranate, we will note any adverse effect from pomegranate extract, such as enhanced oxidative stress, increased fibrin deposition as a sign of injury, or diminished terminal villi lower than control.

Infant Neurobehavior: All infants will have a formal Dubowitz neurologic exam and an attention evaluation using the Hammersmith Neonatal Neurological Examination Optimality score at term equivalent (38-41 weeks post menstrual age). Furthermore, formal neurodevelopmental follow up will take place at 18-24 months of age.

MRI Evaluation

If clinically stable, MRI will be undertaken without sedation at term equivalent (38-41 weeks CGA). The MRI evaluation will include the following analysis:

a) Systematic qualitative scoring of the nature and extent of brain injury

b) Diffusion analysis of the cortical, white matter and posterior limb of the internal capsule to generate apparent diffusion coefficients (ADC).

c) Spectroscopy over the left basal ganglia

d) Brain metrics measuring the length of certain regions of the brain and comparing to standardized values

e) Assessment of MRI developmental indices such as volume and surface folding (SBM)

| **Measure** | **White Matter** | **Gray Matter** |
| --- | --- | --- |
| Qualitative | WM lesion score/  ventriculomegaly | Cortical and DNGM injury score |
| Metrics | Frontal lobe volume, | Intrahemispheric volume loss, ventricular size |
| Volumetry | Total myelinated and unmyelinated WM volumes | Total cortical gray matter, DNGM and CSF volumes  Hippocampal volume |
| Diffusion | Two measures (ADC, RA) each measured on 8 pairs of volume –derived lesions | Two measures (ADC, RA) on:   1. 6 pairs of surface-based regions 2. 8 pairs of volume-derived regions |
| MRS | N/A | Lactate and NAA measures over the L basal ganglia |
| SBM | NA | Four measures (cortical surface area, average sulcal depth, integrating folding index, and percentage buried cortex) |

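### Neither primary outcome counts death, brain injury can be scored only in infants stable enough for MRI, and Table 2's ultrasound criterion matches neither the text nor the schedule

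*Protocol*

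**What the plan says.** Under Biostatistical Analyses, General methods: "The primary outcomes will be either a) brain injury or b) delayed development at 18-24 months". The injury definition opens "Brain injury will be defined as any of the following (see Table 3") and lists four criteria: qualitative injury score, diffusion, spectroscopy, and a group of metrics, volumes and surface measures. All four are MRI measures. Delayed development is "BSID III (MDI or PDI) > 2 SD (< 70) below the normal population".

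Under MRI Evaluation in the Study plan: "If clinically stable, MRI will be undertaken without sedation at term equivalent (38-41 weeks CGA"). The neurological examination described just before it is planned for every infant, with no such condition.

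In the Background (A potential model), growth-restricted infants are said to be "ten times more likely to die in the neonatal period". The same section reports on the pilot of 41 randomised mothers: "We were able to undertake MRI scans in 30 infants due to problems with preterm birth or movement on the MRI".

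The only definition table is headed "Table 2. Definition of CNS Injury by US/ MRI". Its ultrasound row reads "Grade IVH | Low | Grade 2-4". Table 1, the schedule, has no cranial ultrasound. IVH otherwise appears only in the perinatal data list, as an example of morbidity in infants admitted to intensive or special care. Death, fetal or infant, does not appear under Outcome measures.

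**The concern.** Allocation happens during pregnancy and the primaries are measured weeks to two years after birth. A fetus or infant who dies in between cannot have an MRI at term equivalent or a Bayley score, so the protocol gives that pregnancy no outcome on either primary. If such cases drop out, the arms are compared among survivors. If they are coded as not injured, a death counts as a good result.

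The brain-injury primary has a second filter. Being stable enough to scan is itself a state after randomisation, and the treatment is meant to improve it. The protocol also lists preterm labor and gestation at delivery as outcomes, and it names preterm birth as one reason pilot scans were lost.

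The ultrasound row could act the other way. If Table 2 governs, only infants imaged for clinical reasons can be positive on that criterion, so detection would depend on being ill enough to be imaged.

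The results are meant to inform a bigger trial. An event rate taken from survivors only, or an ambiguous injury definition, would carry into that trial's endpoint and sample size.

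**Working it through.** The protocol states no alpha, power, event rate or expected scan count, so there is no figure to reproduce. The check compares the text with itself and then shows scale under stated assumptions.

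**1. Who can be scored on each primary**

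- Brain injury (bullets): alive, stable and scanned at 38-41 weeks.
- Brain injury (Table 2): as above, or positive on an ultrasound that the protocol does not schedule.
- Delayed development: alive and assessed at 18-24 months. There is no MRI or stability condition.
- Death: not an event in either primary, and not a listed outcome.

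**2. Text against table.** The bullets contain no ultrasound item and cite a Table 3 that does not appear in the document. Table 2 contains ultrasound IVH grade 2-4. Whether IVH enters the primary therefore cannot be settled from the document.

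**3. Deaths without a status.** The tenfold figure is relative and no baseline is given, so the death rate *d* is an assumption. Expected deaths = 80 × *d*:

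- 2%: 80 × 0.02 = 1.6
- 5%: 80 × 0.05 = 4
- 10%: 80 × 0.10 = 8

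**4. Scan yield.** Pilot: 30/41 = 73.2% (exact 95% interval 57.1% to 85.8%). Applied to 80: 80 × 0.732 = 58.5, about 59 scans or 29 per arm. The interval gives 45.6 to 68.6, which reflects uncertainty in the pilot proportion only. It leaves out chance variation in the new trial, so it is too narrow as a forecast.

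**5. What selective scanning could do.** Let *p* be the true risk of injury or death, *m* the share unscanned and *q* the risk among the unscanned. The rate among the scanned is (*p* − *m* × *q*)/(1 − *m*). Assume *p* = 50% in both arms (no treatment effect) and *q* from 70% to 100%.

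- Equal loss, *m* = 27% in both arms: (0.50 − 0.27 × 0.70)/0.73 = 42.6%, falling to (0.50 − 0.27 × 1.00)/0.73 = 31.5%. The rate is understated equally in both arms and no false difference appears.
- Unequal loss, 20% against 34%:
  - at *q* = 70%, 0.36/0.80 = 45.0% against 0.262/0.66 = 39.7%, a false difference of 5.3 points;
  - at *q* = 100%, 0.30/0.80 = 37.5% against 0.16/0.66 = 24.2%, a false difference of 13.3 points.

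Nothing in the document says that loss will be unequal. These figures show only what would follow if it were.

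**The case against.** Several stronger readings are tempting, and the document does not support them.

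- *Both primaries are restricted to infants well enough to scan.* They are not. The stability condition applies to MRI only; delayed development depends on survival and attendance. For brain injury, the protocol names no analysis population, so dropping unscanned infants is an inference. What is certain is that the definition gives them no status.
- *The pilot shows that scanning depends on how sick the infant is.* The 11 lost scans (41 − 30) are put down to preterm birth or movement, with no split given. Death and instability are not mentioned, and movement in an unsedated scan is not shown to track illness.
- *The protocol counts on 80 scans.* It says 80 women will be randomised and gives no expected MRI number, so there is no count to correct.
- *Analysing survivors would turn benefit into harm.* Examples can be built in which the sign flips, but they need death and delay rates that the document does not give. With about 40 per arm, they turn on very few infants.
- *The primary already counts IVH.* The bullets do not. Table 2 itself rates the likelihood of that finding as low, so few infants would be reclassified. The fault is a contradiction between text and table, not a demonstrated bias.

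It can also be said that this is a pilot, that a composite with death is not the only valid choice, and that handling of missing scans belongs in an analysis plan that is not at hand. The last point stands in full. The other two temper the severity, but what a primary outcome counts is fixed in the protocol, and here it leaves death without a place.

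**Conclusion.** The point holds within these limits. Death is in neither primary and is not a listed outcome, in a population that the protocol itself describes as at high risk of neonatal death and that is randomised before birth. The brain-injury primary depends in addition on clinical stability at term equivalent. Table 2 disagrees with the bulleted definition and with Table 1 on ultrasound IVH.

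The size cannot be derived from the document. At assumed death rates of 2% to 10%, roughly 2 to 8 of 80 pregnancies have no defined result. The direction is also open: selective MRI would tend to hide injury in the sickest infants, while clinically driven ultrasound would tend to reveal it in them. Balanced loss creates no false difference when there is no effect. The changes should be made, but nothing here shows that the comparison will be biased by any particular amount.

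**What to change.** - Redefine the primaries as *death (fetal or infant, after randomisation) or brain injury* and *death or delayed development at 18-24 months*, in all randomised pregnancies. State the time up to which death counts in each.
- Add death to Outcome measures and report it separately by arm, alongside brain injury and delay. The composite mixes events of different gravity, so it should not be read without its components.
- Reconcile Table 2 with the bullets: take ultrasound IVH out of the primary definition, report it as a clinical outcome from the perinatal data already collected, and correct the reference to Table 3.

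The cost is wording plus one vital-status item in data collection. No new procedures are needed, and who is scanned does not change. The composite settles the status of deaths only. Survivors without MRI remain missing on brain injury, and the method for them can be left to the SAP.
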